# The MAKS-s study: multicomponent non-pharmacological intervention for people with severe dementia in inpatient care – study protocol of a randomised controlled trial

**DOI:** 10.1186/s12877-020-01807-1

**Published:** 2020-10-15

**Keywords:** Severe dementia, Psychosocial intervention, Behavioural and psychological symptoms of dementia, Quality of life, Nursing home, RCT

## Abstract

**Background:**

Nursing homes accommodate a large number of people with severe dementia. More than 80% of residents with dementia suffer from behavioural and psychological symptoms, that can have consequences on the perceived burden of the formal caregivers. Internationally, the number of studies on non-pharmacological interventions for people with severe dementia is very small. One way to reduce these symptoms is to meet the needs of people with severe dementia. The non-pharmacological group intervention MAKS-s, which we will investigate in this study, is intended to reduce the behavioural and psychological symptoms and to improve the quality of life of such people. Additionally, we will investigate the effects on the burden carried by formal caregivers.

**Methods:**

With the present study, we will investigate the effectiveness of a multicomponent non-pharmacological intervention for people with severe dementia living in nursing homes (primary target group). A power analysis indicated that 144 dementia participants should initially be included. In addition, a secondary target group (nursing home staff) will be examined with respect to their dementia-related stress experiences. The study will be conducted as a cluster randomised controlled trail in Germany with a 6-month intervention phase. The nursing homes in the waitlist control group will provide “care as usual.” The primary endpoints of the study will be the behavioural and psychological symptoms of dementia and the quality of life of people with severe dementia. The total duration of the study will be 18 months. Data will be collected by using observer rating scales.

**Discussion:**

The project has some outstanding quality features. The external validity is high, because it is situated in a naturalistic setting in nursing homes and is being carried out with available nursing employees. Due to this fact, a permanent implementation also seems to be possible. Since the participating nursing homes are disseminated across several German federal states and rural and urban regions, the results should be transferable to the entire population.

**Trial registration:**

ISRCTN15722923 (Registration date: 07 August 2019).

## Background

In Europe, more than one third of residents in nursing homes suffer from severe dementia [1–3]. A lack of meaningful occupation is often reported, especially for individuals with moderately severe and severe dementia in nursing homes [4]. Nevertheless, there are very few therapy options for this particularly vulnerable group of people. If at all, individual therapy is considered in relation to people with severe dementia (PWSDs). Guidelines for treating dementia and ecpecially for dealing with challenging behaviour in people with dementia have been published in several countries [5–7]. Only individual interventions for PWSDs are described there, a group intervention is missing from the list. The number of studies on interventions for PWSDs, especially those with high-quality study designs, is very low internationally [8]. This means that either no such approaches have been developed so far, or they have not been published internationally. To date, despite the finding that multicomponent interventions are more effective than single interventions [9], no studies have been conducted on a multicomponent group therapy adapted to the needs of PWSDs. In particular, there is no intervention concept with concrete goals and a structured manual for PWSDs.

The multicomponent MAKS intervention (standing for Motor stimulation, Activities of daily living stimulation, Cognitive stimulation, and Social functioning) was already scientifically approved in two RCTs [10, 11] for its effectiveness on psychological symptoms in people with mild to moderate dementia. We adapted this concept to address the needs of PWSDs. As Cohen-Mansfield and colleagues postulate, understanding unsatisfied needs and finding a remedy should be the starting point of any non-pharmacological intervention [12]. The “Unmet needs model” [12] assumes that dementia patients, due to their cognitive and motivational limitations, become less and less able to communicate and to meet their own needs. This leaves many needs unfulfilled. This frustration and the inability to express oneself verbally contributes to the frequently observed behavioural and psychological symptoms of dementia (BPSD) [12]. Symptoms such as apathy, depression, and anxiety, but also verbal or physical aggression, aberrant motor behaviour, and disinhibition can be interpreted as expressions of this suffering [7]. According to numerous studies, it can be assumed that, over the course of the disease, at least one of these symptoms will affect nearly all individuals with dementia [13, 14] Therefore, the most important goal of non-pharmacological intervention for PWSDs should be to reduce BPSD. Cohen-Mansfield’s [15] research group was able to show positive effects on agitated behavioural symptoms by identifying individuals’ needs and then treating them with specially tailored interventions.

Because behavioural symptoms cause tremendous distress in PWSDs, they consequently influence the quality of life (Qol) of these individuals. This means that in terms of research on quality of life, reducing BPSD also seems to be an important goal. The frequently discussed question here is: Which factors influence the Qol of people with dementia? O’Rourke and colleagues identified four factors that influence the Qol of people with dementia: relationships (together vs. alone), agency in life today (purposeful vs. aimless), wellness perspective (well vs. ill), and sense of place (located vs. unsettled) [16]. Hence, these factors should also be addressed by a non-pharmacological intervention for PWSDs.

In fact, more than 80% of the cognitively impaired individuals in nursing homes suffer from BPSD [17]. With regard to the perspective of nursing staff, this means that BPSD “occur very frequently in the everyday work of nursing staff and represent a far greater burden for them than cognitive impairments” [18] . Three quarters of all nursing staff have to deal with verbally conspicuous and physically restless behavior on a daily basis. Up to 40% of working time is spent on managing BPSD [19]. A total of 26.8% of nursing staff feel burdened by these symptoms [20]. Due to this work related stress factors, health care workers have the greatest incidences in days spent unable to work [21].

Many professional caregivers frequently request practicable activation programmes for PWSDs, as these individuals are often difficult to integrate into existing group settings [22]. Mostly, PWSDs are treated in short units of individual occupation, for example, by applying basal stimulation or by administering snoezelen, although the evidence that these treatments work has been inconclusive [23, 24]. Both are one-on-one interventions and do not fulfil the needs for participation and meaningful activities in a group, social interaction, and social exchange. Cohen-Mansfield [12] identified, among other things, social interaction and meaningful occupation as the most important unmet needs of PWSDs, as well as sensory stimulation. Sakamoto and colleagues [25] also found that interactive involvement is more promising than passive involvement.

This is exactly where MAKS comes in. Through the use of a group setting and multimodality, it is possible to satisfy essential basic human needs, such as the needs for participation, movement, feelings of success, and meaningful activity. By satisfying these elementary needs, BPSD are reduced. Thus MAKS as a psychosocial intervention, represents the instrument of choice for reducing BPSD. Overshott and Burns [8] also came to the conclusion that psychosocial interventions offer an alternative to drug therapy for BPSD with very few side effects.

The objective of this paper is to describe the study protocol of the cluster-randomised MAKS-s study (**MAKS** for people with **s**evere dementia) by following the evidence-based reporting guidelines of the SPIRIT Statement [26].

## Methods/design

### Aims and hypotheses

The main aim of the MAKS-s study, which began in July 2019, is to find out whether a non-pharmacological intervention adapted to the special needs of PWSDs can reduce the BPSD of this target group (primary target group) and consequently improve their Qol. In addition, we expect that the intervention will enable the maintenance of basal activities of daily living (ADLs). There is also the possibility that this improvement will provide some relief for the formal caregivers (secondary target group), which will be shown in a reduction in the number of days spent unable to work.

Research hypotheses:

Based on the primary outcome:
I.By participating in MAKS-s, the BPSD and Qol of PWSDswill be significantly better in the intervention group than in the control group.

Based on the secondary outcome:
II.By participating in MAKS-s, the everyday practical skills of PWSDswill be significantly better in the intervention group than in the control group.III.In the care facilities in which MAKS-s is conducted, the dementia-related stress experience of the nursing and care staff (secondary target group) involved in the care of the participants will be significantly better in comparison with the nursing and care staff in the control facilities.IV.The assumed positive trend described in Hypothesis 3 will lead to a relevant reduction in the number of days spent unable to work for this group of individuals.

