Six months after baseline, the care staff for the control group will receive the same training on how to implement the MAKS-s intervention as the care staff for the intervention group. After the 6-month intervention phase, the intervention and the control groups will be free to decide whether to continue or to begin the MAKS-s intervention, respectively.

The observation period will last 12 months, with a total of four measurement points (baseline, 2, 6, and 12-month follow ups).

The data will be collected by means of nursing home documents, psychometric tests, and external rating scales (see the “Measures” section). All procedures were approved by the Friedrich-Alexander University Erlangen-Nürnberg Ethics Committee. The external GKV Spitzenverband (the institution providing funding) is being regularly informed of the progress of the study and the milestones that have been achieved as set forth in the trial application. The SPIRIT participant timeline is presented in Table 1. When important protocol modifications are required, we will inform the Ethics Committee, the funding institution, the nursing homes, and the platform for the trial registry. The trial registration data are displayed in Table 2.

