Study type	Cluster-randomized controlled multi-center intervention study
Date of first enrollment	01/12/2019
Target sample size	144
Recruitment status	ongoing
Primary outcome(s)	1. Quality of life, measured by QUALIDEM 2. Behavioural and psychological symptoms of dementia, measured by Neuropsychiatric Inventory Nursing Home Version (NPI-NH)
Key secondary outcomes	1. Activities of daily living measured by ADCS-ADL-severe 2. Dementia-related caregiver burden of the nursing and care staff, measured by Professional Care Team Burden Scale (PTCB) 3. Days of incapacity for work of nursing and care staff, measured by documentation of the employer 4. Extent of implementation and voluntary continuation of the intervention in follow-up period, measured by a self-developed questionnaire

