### Sample size estimation

#### Primary target group

A power analysis was computed on the basis of the authors’ previous experience with the pilot study MAKS-s ([name]: Modification and implementation of the MAKS-aktiv! therapy with severrly demented people: a pilot experiment, unpublished master´s thesis, Friedrich-Alexander University Erlangen-Nürnberg). For this purpose, the effects of the subscales “mood”, “disturbing behaviour”, and “social behaviour” of the NOSGER (“Nurses’ Observation Scale for Geriatric Patients”) [27] were pooled. The result was an effect size of Cohen’s *d* = 0.52. The beta-error was set to four times the size of the alpha error (α = .05), as proposed by Cohen [28]. This resulted in a power of .80.

Under these conditions, an evaluation sample of 114 individuals (57 per group, 6 per nursing-home) was deemed necessary. On the basis of the previous MAKS study [10], we expect a drop-out rate (mainly caused by death or being bed-ridden) of 20% across 6 months. This means a total of 144 people with severe dementia has to be included in the study. To achieve this goal, only nursing homes with at least 40 residents are being included in the project. This could be deduced from the following considerations:
In nursing homes in Germany, 38.8% of residents suffer from severe dementia [1]. This means 15 out of 40 individuals.In the “MAKS aktiv” study, the rate of bedridden and/or blind/deaf residents was 26% [10]. In the group of severe dementia cases, this rate was 40%. This left 9 of the 15 people with severe dementia suitable for intervention.It can be assumed that at least 70% of the participants will be willing to participate after the legal representatives have been informed [10]. Thus, 6 of the 9 suitable PWSDs can be included in the study.

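### The single alpha of .05 and power of .80 hold for one endpoint only, but the primary hypothesis joins two unranked primary endpoints and no success rule links them

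*Protocol article*

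**What the plan says.** The abstract of the protocol article declares two primary endpoints: "The primary endpoints of the study will be the behavioural and psychological symptoms of dementia and the quality of life of people with severe dementia". Table 2 (registration data) lists the same two in the opposite order: "1. Quality of life, measured by QUALIDEM 2. Behavioural and psychological symptoms of dementia, measured by Neuropsychiatric Inventory Nursing Home Version (NPI-NH". Neither place ranks them. Under Aims and hypotheses, Hypothesis I covers both in one statement: "the BPSD and Qol of PWSDswill be significantly better in the intervention group than in the control group".

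The section Sample size estimation, Primary target group, describes one comparison. The effect comes from pooling "the effects of the subscales “mood”, “disturbing behaviour”, and “social behaviour” of the NOSGER" in a pilot study: "The result was an effect size of Cohen’s *d* = 0.52". On the error rates it says "The beta-error was set to four times the size of the alpha error (α = .05), as proposed by Cohen" and then "This resulted in a power of .80". The result is 114 evaluable residents, 57 per group, and 144 recruited to allow for 20% drop-out over six months.

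The Data analysis section says that Hypotheses 1 to 3 are tested by multiple regression. It does not say whether one or both endpoints must be significant. On timing, Study design and setting describes a 12-month observation period "with a total of four measurement points (baseline, 2, 6, and 12-month follow ups". It also says that after the 6-month intervention phase control homes may begin MAKS-s if they wish.

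**The concern.** A stated power is a probability of meeting a stated success criterion. Here the criterion in Hypothesis I involves two endpoints, while the power calculation involves one. If the word joining the endpoints is meant as written, the probability of confirming Hypothesis I is lower than the section says. If it is meant loosely, so that either endpoint would do, the chance of a false positive primary result is higher than .05.

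A split result is quite likely in practice. If the intervention truly works on both endpoints with .80 power each, exactly one is significant in about 32% of trials at correlation 0, 23% at 0.5 and 10% at 0.9. For such a result the article's only guide is the wording of Hypothesis I, and its power calculation does not follow that wording.

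**Working it through.** **Inputs from the article.** d = 0.52 (SD scaled to 1), alpha .05, power .80, 57 per group, 20% drop-out, 144 recruited. Sidedness is not stated. Two-sided is assumed, because a one-sided test needs only 46 per group.

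**Inputs assumed.** The effect of 0.52 applies to both endpoints. It was derived on the NOSGER, which is neither primary instrument. The correlation ρ between the two test statistics is not given, so 0 to 0.9 is shown.

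**Step 1: reproduce the article's figures.**
- n per group = 2 × ((1.960 + 0.842) / 0.52)² = 58.05, rounded up to 59, against 57 stated.
- Power at 57 per group: 0.52 × √(57/2) = 2.776, and Φ(2.776 − 1.960) = .793. The noncentral t gives .786.
- Drop-out: 114 / 0.80 = 142.5, so 143. Twenty-four homes × 6 residents = 144.

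The stated figures therefore match one two-sided test of one endpoint, to within rounding. Nothing in them allows for a second endpoint.

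**Step 2: both endpoints required, each at .05.** The familywise error stays at or below .05. Joint power = P(Z₁ > 1.960 and Z₂ > 1.960) under a bivariate normal with correlation ρ. At ρ = 0 and .80 per endpoint this is 0.80² = .64.

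**Step 3: either endpoint sufficient, each at .05, no adjustment.** Familywise error = 1 − P(|Z₁| ≤ 1.960 and |Z₂| ≤ 1.960). At ρ = 0 this is 1 − 0.95² = .0975.

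| ρ | Joint power, .80 per endpoint | Joint power, 57 per group (.793 each) | Familywise error, either rule |
|---|---|---|---|
| 0 | .640 | .628 | 9.75% |
| 0.3 | .666 | .656 | 9.5% |
| 0.5 | .687 | .677 | 9.1% |
| 0.7 | .713 | .704 | 8.3% |
| 0.9 | .750 | .742 | 7.0% |

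With the noncentral t value of .786 per endpoint, joint power at 57 per group is about .62 to .73.

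**Step 4: rules that control alpha in other ways.**
- Fixed sequence, each at .05: familywise error is .05 and power for the first endpoint is unchanged at about .79.
- Bonferroni, .025 each: power per endpoint is about .70 at 57 per group. Power for at least one endpoint is .91 (ρ = 0), .85 (0.5), .81 (0.7) and .77 (0.9). Holm has the same chance of at least one success, and Hochberg's is no lower.

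**Step 5: size needed if both are required at 80% joint power.** 77, 73 or 66 per group at ρ = 0, 0.5 or 0.9. That is 154, 146 or 132 evaluable, and dividing by 0.80 gives 193, 183 or 165 recruited, against 144 planned.

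All figures are before any allowance for clustering by nursing home.

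**The case against.** The strongest reply is that multiplicity rules usually belong in the analysis plan, which is not shown, and that this is a condensed article. That disposes of a complaint about mere silence. It does not dispose of the mismatch: the article itself states both the hypothesis and the power, and the power does not fit the hypothesis as worded. A later plan can add a testing rule, but it cannot raise joint power to .80 with the same 144 residents.

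A reader might go further and infer that either the 5% or the 80% must be false. The documents do not support that. A fixed sequence keeps 5% and about .79 for the first endpoint, and the article leans towards such an order: the Aims present better quality of life as a consequence of reduced BPSD, and the Discussion treats reducing BPSD as the chief goal. An alpha split also keeps the chance of at least one success at or above .80 up to a correlation of about 0.7. Neither rule is stated, however, and both depart from the conjunction in Hypothesis I.

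It is also fair to say that, read literally, Hypothesis I controls alpha and is not met by one significant endpoint. The inflation figures then do not apply, and the shortfall in power is what remains.

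Finally, a reader might infer that there is no primary time point, and that two endpoints at three follow-ups give an error of 1 − 0.95⁶ = 26%. The text points to six months throughout: the intervention phase, the drop-out allowance, and an intention-to-treat set defined by survival to the end of the intervention. No section describes six confirmatory tests, repeated measures on the same residents are not independent, and the timing table (Table 1) is not visible. That figure should not be used.

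**Conclusion.** The concern holds in a limited form. The alpha of .05 and power of .80 are correct, to rounding, for one two-sided test of one endpoint, and they are tied to no rule for the two primary endpoints. Under the literal reading of Hypothesis I, alpha is kept and power is about .64 to .75 with .80 per endpoint (.63 to .74 at 57 per group by the normal approximation), so the stated .80 is not delivered for that hypothesis. Under an unadjusted either-endpoint reading, familywise error is about 9.75% to 7.0%. Both ranges run over assumed correlations of 0 to 0.9. The power range also assumes that the pilot effect of 0.52 applies to each instrument.

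The time point is a labelling gap only: six months is clearly implied but not named as primary. The 12-month comparison is not cleanly randomised treatment against usual care, because control homes may have begun MAKS-s by then. The article does not, however, call it confirmatory.

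**What to change.** Before unblinded analysis, state one success rule in the plan and the registry entry:

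- **Both required.** Each endpoint is tested at .05 with no alpha split, and joint power is restated as about .64 to .75 before any clustering allowance. This matches Hypothesis I as written.
- **Either suffices.** Holm or Hochberg is applied over the two tests, with per-endpoint power of about .70 quoted for a test at .025.
- **Fixed sequence.** For example, BPSD first, in line with the stated main aim, then quality of life, with the .80 attached to the first endpoint only. Hypothesis I should then be reworded to match.

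Under any of these, label the 6-month NPI-NH total and QUALIDEM global score as the primary variables, and describe the 12-month comparison as non-confirmatory.

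The cost is a few sentences and either a lower quoted power or a slightly stricter threshold. This makes the claim accurate but does not restore .80 under the both-required rule. That would take about 165 to 193 recruits, again before clustering.

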### Study design and setting

A two-armed cluster-randomised, controlled, multicentre, prospective longitudinal study with a waitlist control group design will be conducted to test the abovementioned hypotheses.

The nursing homes are located in five areas (German federal state): Bavaria, Baden-Württemberg, Thuringia, Rhineland-Palatinate, and Saarland. All nursing homes (clusters) participating in the study will be randomly assigned to the intervention or control groups at baseline (through random selection) by our cooperation partner “Institut für Medizininformatik, Biometrie und Epidemiologie (IMBE)” at the Friedrich-Alexander University Erlangen-Nürnberg. The clusters will be allocated by applying a tree-step stratification process by using “protective versus non-protective ward”, “area”, and “nursing home size” in decreasing order to balance the structural parameters.

The contact people in each nursing home are trained by the study headquarters with respect to the study protocol, instruments, and screening procedure before randomisation. Informed consent from the legal representatives of the PWSDs and the nursing staff (i.e., trained nurses) and care staff (i.e., staff with no medical training) will also be obtained before randomisation. Nursing homes will be informed about their group assignment in written form by the study headquarters. In addition, the nursing homes in the intervention group will receive further training on the implementation of the MAKS-s intervention. This treatment will be performed through the 6-month intervention phase. The nursing homes in the control group will not carry out any specific treatment but will continue providing “care as usual”.

Because we are investigating a non-pharmacological intervention, not everybody participating in the study can be blinded. Due to the severity of dementia, we can assume that the PWSDs will be blind to the conditions of the study. The therapists performing the MAKS-s intervention cannot be blinded. The raters (nursing staff) will be “semi-blinded”. They will know about the group assignment but will have no knowledge of the intervention. The testers, who are trained students from the study headquarters, who will conduct the tests, will be completely blinded.

Six months after baseline, the care staff for the control group will receive the same training on how to implement the MAKS-s intervention as the care staff for the intervention group. After the 6-month intervention phase, the intervention and the control groups will be free to decide whether to continue or to begin the MAKS-s intervention, respectively.

The observation period will last 12 months, with a total of four measurement points (baseline, 2, 6, and 12-month follow ups).

The data will be collected by means of nursing home documents, psychometric tests, and external rating scales (see the “Measures” section). All procedures were approved by the Friedrich-Alexander University Erlangen-Nürnberg Ethics Committee. The external GKV Spitzenverband (the institution providing funding) is being regularly informed of the progress of the study and the milestones that have been achieved as set forth in the trial application. The SPIRIT participant timeline is presented in Table 1. When important protocol modifications are required, we will inform the Ethics Committee, the funding institution, the nursing homes, and the platform for the trial registry. The trial registration data are displayed in Table 2.

